## Methods/Design

### Design

The proposed study will be a prospective cohort study comprised of a five-month training period followed by six-month run-in (could be shorter if no issues are identified) and 36-month evaluation periods in Ottawa, Canada. During the training period, paramedics will not actually clear the c-spine. During the 'run-in' and 'evaluation' periods, the paramedics will then be empowered by medical directive from the EMS medical directors and the Ministry of Health to "clear" the c-spine of patients according to the CCR. This will allow the paramedics to selectively transport low-risk trauma patients to the ED without full spinal immobilization. We will employ the run-in period immediately prior to the onset of the 'evaluation' period, to resolve logistical issues for the new practice of paramedics applying the CCR in the field. We will compare outcomes in the evaluation period of this study to those during the validation study at the same site (Ottawa) [77].

### Study population

#### Inclusion Criteria

We will enroll consecutive alert, stable adults evaluated by the paramedics with potential c-spine injury after sustaining acute blunt trauma. These are patients for whom standard EMS protocols require immobilization. Patient eligibility will be determined at the time of paramedic arrival at the scene based on the following criteria:

a) "Potential c-spine injury after sustaining acute blunt trauma" will include patients with either: i) neck pain with any mechanism of injury (subjective complaint by the patient of any pain in the posterior aspect of the neck),

ii) no neck pain but some visible injury above the clavicles, and/or

iii) neither neck pain nor visible injury, but significant mechanism of injury as determined by the paramedic at the scene.

b) "Alert" is defined as a Glasgow Coma Scale [80] score of 15 (converses, fully oriented, and follows commands).

c) "Stable" refers to normal vital signs as defined by the Revised Trauma Score [7] (systolic blood pressure 90 mm Hg or greater and respiratory rate between 10 and 24 breaths per minute).

d) "Acute" refers to injury within the past 4 hours.

#### Exclusion Criteria

a) Patients under the age of 16 years,

b) Patients with penetrating trauma from stabbing or gunshot wound,

c) Patients with acute paralysis (paraplegia, quadriplegia),

d) Patients with known vertebral disease (ankylosing spondylitis, rheumatoid arthritis, spinal stenosis, or previous cervical spine surgery), or

e) Patients referred from another hospital and transported between facilities.

#### Comparison Group from the Validation Study

We will quantify the potential impact of selective prehospital immobilization by way of comparison with a convenience sample of patients recruited in Ottawa during the validation of the CCR by paramedics between 2002 and 2006 [77]. These participants were recruited using the exact same criteria, and represent 862 of the 1949 recruited in the validation study [77].

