### Validation of the CCR by paramedics

The validation of the CCR by paramedics took place between 2002 and 2006 in seven EMS systems distributed in three Canadian provinces [77]. The study population consisted of consecutive alert, stable, and cooperative adults transported by ambulance to the local lead trauma hospital after sustaining acute blunt trauma with potential injury to the neck. These are patients for whom standard basic trauma life support (BTLS) protocols require immobilization. Patient assessment was made by primary care or advanced care paramedics, who were trained by means of a 2-hour web-based training session followed by a practical demonstration to assess the CCR and the component clinical variables in a uniform manner. The paramedics recorded their findings along with their interpretation of the decision rule itself on a data collection form prior to arrival at hospital. They followed standard procedures for immobilization of patients and did not use the CCR as the basis for the decision to immobilize. The primary outcome, acute cervical spine injury, was defined as any fracture, dislocation, or ligamentous instability demonstrated on radiography. A clinically important cervical spine injury was defined as any injury requiring internal fixation or treatment with a halo, brace, or rigid collar. All enrolled patients who did not have radiography received telephone follow-up and were classified as having no acute cervical spine injury if they met all the previously validated explicit criteria at 14 days [78].

We enrolled 2,393 eligible patients in the study. 1,126 patients were not evaluated with radiography, and required telephone follow-up. We reached 788 (70.0%) of those patients, among which 682 were determined to not have sustained a cervical spine injury according to our validated proxy assessment tool. A total of 1,949 enrolled patients had complete outcome assessments. Twelve (0.6%) had a clinically important cervical-spine injury. In two cases, the investigators could perform an independent assessment of the rule based on the paramedic care report, but could not evaluate the paramedic assessment of the rule based on their study data collection sheet. The characteristics of the 444 patients without outcome assessments were similar to those with radiographic evaluation, but were less likely to be admitted to the hospital.

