#### Measures of safety (primary study outcomes)

a) Number of missed cervical spine injuries, i.e. number of clinically important c-spine injuries (as defined previously) identified in patients who have had their c-spine cleared by paramedics. We will know the presence of fracture or cervical spine injury from review of diagnostic imaging reports in the patient record. We also propose to institute a strategy of surveillance to identify the uncommon occurrence of a fracture missed because no radiography was ordered. ED Patient Visit Logs at each receiving hospitals will be monitored for 30 days to identify return visits by patients who do not undergo radiography during their initial ED visit. In addition, we will review the Neurosurgery Patient Logs at our regional neurosurgical centre (The Ottawa Hospital, Civic Campus). This centre provides care for patients with spinal cord injuries for the whole Ottawa region. We recognize that there is a very small risk of not identifying a missed fracture but feel that this approach is pragmatic and feasible.

b) Number of serious adverse outcomes, i.e. development of neurological deficit after c-spine clearance by the paramedics. This very unlikely subset of missed cervical spine injury cases will be determined from review of the patient records. We will monitor for the extremely rare occurrence of motor weakness and disability that develops after paramedic assessment but do not expect this to occur.

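### The Ottawa comparator is a complete-outcome subset described as everyone recruited under identical criteria; this probably lengthens its ED stay and favours the new strategy

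*Protocol article*

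**What the plan says.** The section Comparison Group from the Validation Study defines the historical group: "These participants were recruited using the exact same criteria, and represent 862 of the 1949 recruited in the validation study".

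The Background section Validation of the CCR by paramedics describes the same study differently:

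- Enrolment: "We enrolled 2,393 eligible patients in the study".
- Outcome: "A total of 1,949 enrolled patients had complete outcome assessments".
- Imaging: "1,126 patients were not evaluated with radiography, and required telephone follow-up".
- Telephone follow-up: "We reached 788 (70.0%) of those patients, among which 682 were determined to not have sustained a cervical spine injury".
- Patients left out, in a sentence that ends on hospital admission: "The characteristics of the 444 patients without outcome assessments were similar to those with radiographic evaluation, but were less likely to be admitted to the" (last word cut).
- Destination: the population was adults "transported by ambulance to the local lead trauma hospital after sustaining acute blunt trauma".

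For the new study, the inclusion and exclusion criteria name no destination hospital. The safety outcome section implies more than one: "ED Patient Visit Logs at each receiving hospitals will be monitored for 30 days". Under Measures of clinical impact, times are taken for every patient whom the paramedics assess and enroll, with no condition that an injury outcome was obtained. Under Data analysis, evaluation-phase times are compared with those of the Ottawa validation patients by Student's t-test, and no adjustment is stated. Lengths of time are listed among the primary outcomes.

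**The concern.** The article calls 1,949 the number recruited, but by its own account this is the number left after patients without an injury outcome were removed. That removal was not neutral. It took out only patients who had not been imaged, and the article reports elsewhere that such patients spend much less time in the ED. The evaluation cohort is not filtered in this way. A comparator enriched for imaged patients would tend to show a longer mean ED stay, so part of any observed reduction could come from how the historical group was assembled and not from paramedic clearance.

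The claim of identical criteria also conflicts with the lead trauma hospital restriction in the validation study. Handover time and ED stay both arise in the receiving ED, so a difference in hospital mix matters for a like-for-like comparison, whichever way it acts.

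**Working it through.** **1. Reproduce the 1,949** (inputs from Validation of the CCR by paramedics)

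- Radiographed: 2,393 − 1,126 = 1,267.
- Radiographed plus telephone-cleared: 1,267 + 682 = 1,949, which is exactly the complete-outcome figure.
- Left out: 2,393 − 1,949 = 444. The same number comes from the unradiographed side: (1,126 − 788) not reached + (788 − 682) reached but not cleared = 338 + 106 = 444.

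All 444 therefore come from the unradiographed group. They are 444/2,393 = 18.6% of those enrolled and 444/1,126 = 39.4% of those not imaged.

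**2. Effect on case mix**

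- Radiographed share of all enrolled: 1,267/2,393 = 52.9%.
- Radiographed share of the complete-outcome set: 1,267/1,949 = 65.0%.
- Difference: 12.1 percentage points.

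**3. Translate to ED stay**

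The only stays by imaging status in the article are from the phase II physician cohort (Previous physician Canadian C-Spine Rule studies): 232.9 min with radiography and 123.2 min without, a gap of 109.7 min. Mean stay = share × 232.9 + (1 − share) × 123.2.

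- Complete-outcome set: 0.650 × 232.9 + 0.350 × 123.2 = 194.5 min.
- All enrolled: 0.529 × 232.9 + 0.471 × 123.2 = 181.3 min.
- Shift: 13.2 min.

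If the gap among ambulance patients were smaller, the shift would shrink in proportion: 7.2 min for a 60-min gap and 3.6 min for a 30-min gap.

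**4. Ottawa alone**

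The comparator is 862 Ottawa patients, and Ottawa's share of the 444 is not given. Assume that 65.0% of the 862 were radiographed (about 560) and apply the 109.7-min gap:

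| Ottawa patients left out | Ottawa enrolled | Radiographed share | Shift in mean ED stay |
|---|---|---|---|
| 0 | 862 | 65.0% | 0 min |
| 196 (proportional: 444 × 862/1,949) | 1,058 | 53.0% | 13.2 min |
| 444 (all) | 1,306 | 42.9% | 24.2 min |

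**5. What such a shift does to the planned test**

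The article gives no standard deviation, so a range is assumed. With 862 comparator and 3,000 evaluation patients, SE = SD × √(1/862 + 1/3,000) = 0.0386 × SD. With no true effect and a 13.2-min shift, the two-sided 5% test would reject as follows:

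| Assumed SD (min) | SE (min) | Chance of rejection |
|---|---|---|
| 120 | 4.6 | 81% |
| 180 | 7.0 | 48% |
| 240 | 9.3 | 30% |
| 360 | 13.9 | 16% |

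Each is well above the nominal 5%.

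**The case against.** **The size for Ottawa is unknown.** Ottawa's losses could be few, and the stays come from a physician ED cohort limited to uninjured patients with reliable times, not from immobilized ambulance patients. The article also says that the 444 resembled the radiographed patients apart from admission. This stands. A reader might infer that comparator stays are known to be longer by a definite amount; the documents support only a probable direction and a range that includes zero.

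**The shift may be small beside the hoped-for gain.** The section on cervical spine immobilization contrasts median stays of 8 to 12 hours in the stretcher area with under 4 hours for patients arriving without immobilization. At 40% clearance, that is roughly 0.4 × 240 = 96 to 0.4 × 480 = 192 min pooled, so 13 min would be about 7% to 14% of it. This is illustrative, since those figures are medians. One could instead set the 13 min against the gap by imaging status and reach a larger fraction. That would assume clearance by paramedics removes imaging, which the protocol does not say: imaging remains an ED decision. No fraction of the expected effect is claimed here.

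**The criteria may differ less than they seem to.** The validation summary also describes patients as cooperative, and a reader might count this as another mismatch. The new study's definition of alert (Glasgow Coma Scale 15, following commands) largely covers it. Destination is different: it is stated for one study and absent from the other. The mention of several receiving hospitals comes from the plan for detecting return visits, so the mismatch is inferred, but it fits poorly with a single-destination cohort. A reader might further infer that the trauma hospital restriction lengthens comparator stays. No figure in the article gives that effect a direction.

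**The reach is narrow, and detail may sit elsewhere.** The group is openly called a convenience sample, the study is described as preliminary, and adjustment could be set out in an analysis plan. That is fair as to adjustment. It does not answer the point that the article says who the comparator is and contradicts its own account of that study.

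**Conclusion.** The concern holds in a bounded form. The description of the comparator is wrong on the article's own numbers: 1,949 is a complete-outcome subset of 2,393 enrolled, and the claim of identical criteria conflicts with the destination limit in the validation study. The outcome filter removed only unimaged, less often admitted patients, so it probably lengthens comparator ED stay and tilts that comparison towards the new strategy.

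The size is about 13 min, on the assumptions that the seven-system proportions hold in Ottawa and that the physician-cohort stays carry over. The range is 0 to about 24 min according to Ottawa's share of the losses, and less if the imaging gap is smaller in ambulance patients.

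The quantified bias concerns total ED stay only. Nothing in the article ties it to field time or handover time. It shows no effect on the immobilization comparison, where the comparator is close to 100% by protocol, or on missed injuries. This should be corrected before the time analysis is run, but it does not undermine the study's safety aim.

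**What to change.** 1. In Comparison Group from the Validation Study, describe the 1,949 as the patients with complete outcome assessments, and state how many patients Ottawa enrolled as well as the 862.
2. Delete the statement that the criteria were identical. Set out the known differences: destination hospital and the requirement for a complete outcome.
3. For the time outcomes, define the comparator as all enrolled Ottawa validation patients with retrievable times. Measuring a time interval does not require injury ascertainment, so the outcome filter serves no purpose here.
4. Report the ED-based intervals also by receiving hospital, or restricted to the lead trauma hospital as a sensitivity analysis. It should not replace the main comparison: if clearance influences where patients are taken, the restriction would condition on something decided after the paramedic assessment.

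The cost is wording, plus retrieving times for the omitted Ottawa patients: about 196 if losses were proportional. The article does not say whether those times were recorded, so the sponsor needs to confirm that they are available. If they are not, the comparator should be presented as outcome-filtered and the likely direction of the bias in ED stay stated with the result.

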#### Patient Safety

We are convinced that the use of the CCR is accurate and reliable and that the proposed study will respect patient safety at all times. Paramedics will know that they can 'override' the rule at any time when they have concerns about patient welfare. The CCR has proven to be very sensitive in identifying cervical spine injuries in previous validation studies with paramedics, nurses, and physicians and in the recent implementation study with physicians. With more than 32,000 patients evaluated, the CCR has never missed a single injury resulting in spinal cord injury. Nevertheless, we have included the following strategies to maximize the safety of this study:

1. We have re-designed the new proposal to include only a single centre to focus on safety and efficacy.

2. The single site proposed for this study also participated in the paramedic validation study.

3. Paramedics will only participate in this study if they:

• have completed a 2-hour training session and,

• pass a written test.

4. Paramedics will use the CCR under a medical directive signed by the Ministry of Health.

5. We will have an independent Data Safety Monitoring Committee review results on a regular basis; that committee will have the authority to recommend termination if patient safety is a concern.

#### Ethical Considerations

The study protocol received the approval of The Ottawa Hospital Research Ethics Board (protocol #2009142-01H) without the need for written patient consent. Paramedics will use the CCR under a medical directive, making training and participation in the study mandatory. Because of this, the Research Ethics Board also waived the need for paramedic consent. During a particular period in time, all eligible patients will be managed by the paramedics in the same manner in this observational cohort study. Patients will not be randomized. Patients will not be subjected to new therapy, invasive procedures, undue risk or discomfort, or investigations beyond that which would normally be required in the course of patient care. Patient confidentiality will be maintained throughout the study and patient names will be removed from all records. This is consistent with the approach approved by the Research Ethics Boards for our previous physician, ED triage nurse, and paramedic validation and implementation studies.

### Study interventions

#### Training

Initial training for all paramedics will entail one hour of self-review of a teaching CD, followed by a short quiz, followed by an in-person presentation of scenarios and question and answer. The teaching CD includes continuous audio and video presentation of slides on evidence and application, questions and answers, and case studies. All paramedics will have to successfully complete a written test in order to be certified in c-spine assessment.

#### Run-in period

This phase will allow the paramedics to fully clear the c-spine of low-risk patients. The purpose of the run-in period is to provide pilot experience with clearance and removal of immobilization in order to identify any logistical or unforeseen barriers. This run-in period is necessary since it will represent the first time that paramedics have actually not immobilized low-risk trauma victims in Ottawa, and we wish to proceed cautiously prior to enrolling cases for the study analysis.

#### Evaluation period

As in the run-in period, paramedics will be empowered by local medical directive to assess the c-spine of eligible patients according to the CCR and to selectively withhold immobilization where indicated. This will permit some patients to sit up on the ambulance stretcher and be taken to a low acuity or ambulatory area of the ED, rather than being left on a backboard in a high acuity or trauma area. Paramedics will record their findings on a simple Paramedic Data Form and in their paramedic ambulance care report.

#### Ongoing education

a) Study Champions will be identified among the EMS service. These "champions" will be paramedics who will serve as a local resource for the participating paramedics. The champion will be responsible for initial training, continuing education, and trouble-shooting issues brought up by the paramedics. They also helped recruitment significantly during the validation study.

b) Continuing education will be provided to all paramedics at least every six months and will be done by study champions in the format of small group sessions, such as during daily morning briefings, while the paramedics are on duty.

c) Newsletters will be developed and distributed to all study paramedics on a monthly basis. These will include tips on assessment and feedback on enrollment.

d) Local study champions will monitor staff turnover and ensure that new paramedics are trained for the study in a timely fashion.

### Outcome measures and data collection

#### Data collection

The following outcome data will be collected by dedicated study personnel who will review daily patient logs, ED patient records, diagnostic imaging reports, and in-patient records. All participating paramedics will complete a Paramedic Data Form at the time of each patient assessment as well as document patient care on their province wide Ambulance Call Reports. Additional study data will be recorded on a Case Record Form. All outcomes will be collected during the run-in and evaluation periods, but the run-in data will not be used in the final analysis (this run-in phase may be shortened if no issues are identified).

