#### Performance of the Canadian C-Spine Rule (secondary study outcomes)

The rule will be evaluated during the run-in and evaluation periods for all enrolled cases with completed Paramedic Data Forms.

a) Accuracy of the rule, i.e. sensitivity and specificity for identifying clinically important cervical spine injuries.

b) Paramedic accuracy in overall interpretation of the rule (immobilization required versus no immobilization required) will be determined by comparing the paramedics' response on the data collection form to the 'gold standard' interpretation of the rule made by the Investigators' Steering Committee. Attention will be focused on fractures missed or potentially missed by paramedic misinterpretation.

c) Paramedic agreement and comfort with and use of the rule. Paramedics, on the data collection form, will be asked to indicate their comfort in following the rule for each specific patient, using a five-point Likert scale. If the paramedic decides not to follow the rule, they will be asked to indicate reasons for their decision and if they recommend that additional follow-up and clarification from the study champion would be helpful. Ongoing education at regular intervals is a feature of the intervention and it will be important to address paramedics' concerns about using the decision rule.

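### Run-in data are excluded from the final analysis in one section and included in the rule's evaluation in another, and the exclusion leaves the first real clearances out of the final safety estimate

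*Protocol article*

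**What the plan says.** All statements are in the protocol article.

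- **Design** plans a "six-month run-in (could be shorter if no issues are identified) and 36-month evaluation periods". Paramedics may clear patients in both periods. Outcomes in the evaluation period are to be compared with the earlier validation study at the same site.
- **Run-in period** confirms that clearance is real: "This phase will allow the paramedics to fully clear the c-spine of low-risk patients". It adds that "it will represent the first time that paramedics have actually not immobilized low-risk trauma victims in Ottawa", and gives as the reason for the phase that "we wish to proceed cautiously prior to enrolling cases for the study analysis".
- **Data collection** sets the rule for all outcomes: they are collected in both periods, but "the run-in data will not be used in the final analysis".
- **Performance of the Canadian C-Spine Rule (secondary study outcomes)** opens with a different rule: "The rule will be evaluated during the run-in and evaluation periods for all enrolled cases with completed Paramedic Data Forms". This sentence covers accuracy of the rule, paramedic interpretation, and comfort and use.
- **Measures of safety (primary study outcomes)** counts clinically important injuries, and neurological deficits, in patients cleared by paramedics. It does not mention a period.
- **Data analysis, Measures of safety** compares the validation and evaluation periods and expects a missed-injury rate of 0% in both.
- **Data analysis, Performance of the Canadian C-Spine Rule** defines the accuracy statistics without saying which period supplies the cases.

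**The concern.** There are two linked problems.

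First, the article fixes two incompatible analysis sets for the secondary outcomes. An analyst following Data collection would leave run-in cases out of sensitivity, specificity and paramedic accuracy. An analyst following the section on performance of the rule would put them in. Nothing in the article decides between them.

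Second, a run-in patient cleared by a paramedic meets the definition of the primary safety population in every respect except the calendar. If such a patient proves to have a clinically important injury, it is a real miss. Under the exclusion it would not enter the final missed-injury estimate, yet under the other rule the same case could be discussed among the secondary results, where attention is directed to fractures missed through misinterpretation.

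The Rationale makes demonstrated safety a condition of wider use, and the expected count is zero. When zero is the anticipated answer, one event outside the count changes how the result reads.

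**Working it through.** **Step 1. Do the two sections conflict?** Data collection already says that outcomes are collected in both periods, and then excludes the run-in from the final analysis. The performance section specifies a case set (enrolled cases with completed forms, from both periods). Reading its word for evaluation as mere collection would make it repeat Data collection and would ignore that case set. The analysis section is silent on period. The conflict therefore stands.

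**Step 2. Inputs.**

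- 3,000 patients over 36 months, about 20 clinically important injuries, and up to 40% transported without immobilization (Sample size).
- 12 such injuries in 1,949 patients (Validation of the CCR by paramedics).
- Run-in of up to six months (Design, Sample size).
- Assumptions: the run-in has the same accrual and clearance as the evaluation period, and the missed-injury percentage is taken over cleared patients. The article gives no run-in enrolment figure and no minimum length, so one month is an illustrative short case.

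**Step 3. Reproduce the plan's own figure.** Expected injuries = 3,000 × 12/1,949 = 18.5, close to the stated 20.

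**Step 4. Size of the excluded group.** Accrual = 3,000/36 = 83.3 patients per month. Cleared = patients × 0.40. Injuries = patients × 20/3,000.

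| Run-in | Patients | Cleared | Injuries (cleared or not) | Share of run-in plus evaluation |
|---|---|---|---|---|
| 1 month | 83 | 33 | 0.6 | 83/3,083 = 2.7% |
| 3 months | 250 | 100 | 1.7 | 250/3,250 = 7.7% |
| 6 months (cap) | 500 | 200 | 3.3 | 500/3,500 = 14.3% |

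With the validation rate, the six-month injury figure is 500 × 12/1,949 = 3.1. With the validation study's potential clearance of 100% − 62.2% = 37.8%, the six-month cleared figure is 500 × 0.378 = 189.

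**Step 5. No miss in either period.** The exact two-sided 95% upper limit for zero events is 1 − 0.025^(1/n).

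- Evaluation only, n = 3,000 × 0.40 = 1,200: 1 − 0.025^(1/1,200) = 0.31%.
- With a six-month run-in, n = 1,200 + 200 = 1,400: 1 − 0.025^(1/1,400) = 0.26%.

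**Step 6. One miss in a six-month run-in, none afterwards.**

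- Under the exclusion: 0/1,200, 95% CI 0 to 0.31%.
- Over all cleared patients: 1/1,400 = 0.07%, exact (Clopper-Pearson) 95% CI 0.002% to 0.40%.

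**The case against.** A run-in to settle logistics, set aside in advance, is a legitimate design. The article states its target, which is the evaluation period compared with the validation study, and for the primary outcomes the evaluation period is used consistently. The direct contradiction touches secondary outcomes only. All of this stands, and it is why evaluation-only analysis should remain for clearance proportion, times and the historical comparison.

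Run-in harm would not be invisible either. All outcomes are collected then, and an independent committee reviews results regularly and can recommend termination (Patient Safety). The gap is in the final reported estimate, not in detection or oversight.

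Three stronger readings might be inferred, and the documents do not support them.

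- *The exclusion depends on outcome and biases the safety result towards zero.* Run-in length is tied to undefined issues, described mainly as logistical, and not to missed injuries. A safety event is not ruled out as such an issue, but no link to the missed-injury count is stated. Nor is there evidence of a higher miss rate early on: training and a written test come first, and the service took part in the validation study. Sensitivity in paramedic hands there was 100% (95% CI 74% to 100%), so about 3.1 run-in injuries imply no expected misses at the point estimate and 3.1 × 0.26 = 0.8 at the lower limit.
- *The run-in is prolonged when problems appear.* It is capped at six months and can only be shortened.
- *Each excluded miss shifts sensitivity by five points (1/20).* This does not follow from the safety exclusion. Sensitivity is the outcome for which the performance section includes the run-in, and it uses the investigators' interpretation of the rule, whereas the safety count uses actual clearance. The two can differ even in identical patients.

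**Conclusion.** The point holds as an inconsistency and a reporting gap that should be fixed. The two sections give incompatible rules for the secondary outcomes. As worded, the exclusion also keeps the first patients actually cleared out of the final primary safety estimate.

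The group concerned is at most about 14% of cleared patients and could be under 3% if the run-in is short. The cost in precision is slight. The point matters chiefly in the hypothetical case of a run-in miss, where the final estimate would show no events although one had occurred. The figures rest on planned accrual and 40% clearance carrying over to the run-in; the six-month figures are the maximum case. No outcome-dependent bias has been demonstrated.

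**What to change.** 1. In Data collection, replace the blanket exclusion with a statement of the analysis period for each outcome.
2. Keep the evaluation period alone for clearance proportion, time intervals and the comparison with the validation study.
3. List and count missed injuries and serious adverse outcomes for every patient cleared from the first day of the run-in, with a 95% CI, beside the evaluation-only estimate.
4. Amend the opening sentence of the performance section so that rule performance is reported for the evaluation period, with run-in plus evaluation as a labelled supplementary result.

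The cost is a few sentences and no new data, since every outcome is already collected in the run-in. The downside is that the safety result may look slightly less favourable if a run-in event occurs.
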